#### Effects of Intervention in Phase III

A recent meta-analysis (Zhu et al., 2016) proposed that the estimated combined effect size of physical and cognitive interventions, presented as Cohen’s *d*, is 0.29. In our study, considering α = 0.05, a β = 10 and an annual drop-out of 5%, we will be able to detect in a pre-post repeated measure ANOVA on the different outcomes (e.g., Flanker effect) between two groups of 250 participants a small effect *d* = 0.17.

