### Phase III: Randomized Control Trial of a Multi-Dimensional Lifestyle Intervention

The third phase of the study is aimed to start in 2019 and will consist of a 6-month multi-dimensional intervention, administered via an Information and Communication Technology (ICT)-based platform. Five hundred participants from the general cohort who did not participate in phase II will be invited to participate. Phase III will be a randomized-control trial (RCT) of a multidomain intervention of remotely supervised coach-led lifestyle habits. A control group will consist of participants who receive education regarding healthy lifestyles but no coaching. All participants will undergo the in-person evaluations described in phase II at baseline and following the 6-month intervention. All participants will be monitored using mobile technologies to assess adherence to the multi-dimensional intervention and capture relevant metrics of physical activity, diet, sleep, etc.

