#### Principal Statistical Analysis

Principal statistical analyses to be performed will include mainly linear regression models in within-subjects and between-groups experimental designs. We may require applying non-parametric statistics in certain cases.

We will also use exploratory data mining techniques like clustering and classifiers in order to identify groups of similar participants and explore the relation between different biologic and lifestyles variables and the different outcomes.

The final aim of this study is to investigate and identify those factors that can promote Brain Health. Considering the binary nature of the end-point of this study (phase I and II), the analysis within the study population will be based on the calculation of odds ratios, hazard ratios and relative risks of exposure to protective factors on the *a priori*-defined 7 pillars of interest. All analyses will be performed correcting for covariate variables (e.g., age, sex, education, income, etc.)

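### Phase III is powered on a pre-post repeated-measures ANOVA; adjusting for the baseline value of each outcome would be more precise from the same data

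*Protocol article*

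**What the plan says.** The section Effects of Intervention in Phase III gives the detection limit. It cites a literature effect "presented as Cohen’s *d*, is 0.29". Then, "considering α = 0.05, a β = 10 and an annual drop-out of 5" per cent, it says that "we will be able to detect in a pre-post repeated measure ANOVA on the different outcomes", "between two groups of 250 participants a small effect" of d = 0.17.

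The design section for Phase III says that "Phase III will be a randomized-control trial (RCT) of a multidomain intervention", and on timing: "All participants will undergo the in-person evaluations described in phase II at baseline and following the 6-month intervention". Each outcome therefore has one pre value and one post value.

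The section Principal Statistical Analysis covers the whole initiative. It names chiefly linear regression for within-subject and between-group designs, and adds: "All analyses will be performed correcting for covariate variables (e.g., age, sex, education, income, etc". That list is open, but the baseline value of the outcome is not among the examples. The pre-post correlation is not given anywhere in the article.

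**The concern.** With two visits, the group-by-time term of a repeated-measures ANOVA gives the same test as a t-test on change from baseline. That fixes the coefficient of the baseline value at 1. A linear model of the 6-month value on arm and baseline estimates the coefficient instead, and under equal variances it is rho. When rho is below 1, the change score subtracts too much of any chance baseline difference and carries extra noise.

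Randomisation makes both estimates unbiased, so only precision is at stake. It matters here because the trial looks for small effects on several outcomes, whose correlations will differ. The baseline values are collected in any case.

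**Working it through.** **Inputs.** From the article: 250 per group, alpha 0.05, beta printed as 10, drop-out 5% a year, d = 0.17, literature d = 0.29. Assumed: two-sided test, beta read as 10% (90% power), equal outcome variance at both visits, treatment effect tested by the group-by-time term. The correlation rho is an assumption throughout. The only reliability figure in the article (0.80 or more over about 58 days, section Surveys) is for the Phase I questionnaire, not the Phase III outcomes.

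**Formula.** Detectable difference in outcome SDs = (1.960 + 1.282) × sqrt(2/n) × k, with
- k = 1 for the 6-month value alone,
- k = sqrt(2(1 − rho)) for the change score,
- k = sqrt(1 − rho²) for the baseline-adjusted model (ANCOVA).

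At n = 250 and k = 1: 3.242 × 0.0894 = 0.290.

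**Step 1: the plan's own figure.** The value 0.17 cannot be derived from the stated inputs, because it needs rho. Two readings reproduce it:
- *In outcome SDs.* 0.17 = 0.290 × sqrt(2(1 − rho)) gives rho = 0.83 (0.832 with 2.5% loss over 6 months, 0.837 with 5% loss).
- *As d = 2f from the within-between F test.* Here f = 0.085 and the noncentrality is f² × 500 × 2/(1 − rho) = 7.225/(1 − rho). Solving for 90% power with the noncentral F gives rho = 0.32 (0.33 with 2.5% loss, 0.35 with 5%). On this scale 0.17 is a between-group difference in change of 2 × 0.17 = 0.34 SD.

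The between-group main effect of the same ANOVA does not reproduce 0.17. At 90% power it gives 0.205 or more for any rho of 0 or above.

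**Step 2: precision.** Variance ratio, ANCOVA to change score = (1 − rho²)/(2(1 − rho)) = (1 + rho)/2.

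| rho (assumed) | Change score, detectable SD | ANCOVA, detectable SD | Variance ratio | Reduction |
|---|---|---|---|---|
| 0.3 | 0.343 | 0.277 | 0.65 | 35% |
| 0.5 | 0.290 | 0.251 | 0.75 | 25% |
| 0.7 | 0.225 | 0.207 | 0.85 | 15% |
| 0.8 | 0.183 | 0.174 | 0.90 | 10% |
| 0.83 | 0.169 | 0.162 | 0.915 | 8.5% |

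These are at 250 per group. With 2.5% loss (243.75 per group), the rho 0.5 row becomes 0.294 and 0.254. The ratios do not depend on n.

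**Step 3: the gain under each reading of 0.17.**
- SD units, rho 0.83: sqrt(0.915) = 0.957, so the standard error falls by about 4% and 0.170 becomes about 0.163.
- d = 2f, rho 0.32: sqrt(0.66) = 0.81, so the standard error falls by about 19%.

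**Step 4: power for a true difference of 0.29 SD, 250 per group.** Change score against ANCOVA: 78% and 93% at rho 0.3; 90% and 96% at rho 0.5; 99% and 99.5% at rho 0.7.

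**The case against.** The strongest reply is that the ANOVA appears in a statement of detectable effect, not in the analysis section. The analysis section names linear regression with an open covariate list, which is the class of model recommended here. The section Multi-Dimensional Intervention: Rationale and Characteristics also says that Phase III details were still being settled. This stands in part: the article does not commit Phase III firmly to the ANOVA, and it permits baseline adjustment. But it names one method for Phase III, states its sensitivity on that method, and nowhere names the baseline outcome as a covariate. The point therefore concerns the method that the article does name, and is not a complaint about detail left to another document.

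The reply is also right that the gain may be small. At rho near 0.83 it is about 4% in standard error.

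A reader might infer two stronger points, and neither is supported:
- *That the ANOVA wastes the baseline.* It uses the baseline with a slope of 1, and for rho above 0.5 it already beats a comparison of 6-month values alone.
- *That a better model would bring in participants who have only a baseline visit.* The ANCOVA drops them too. A constrained longitudinal model with a shared baseline mean and common covariance keeps them in the data set. With two visits, though, they inform only the baseline mean, and the treatment effect still comes from those with a 6-month value. At 2.5% loss this concerns about 6 people per group.

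**Conclusion.** The point holds as a matter of efficiency. The group-by-time test is valid, but at every rho below 1 it is less precise than the baseline-adjusted model, by the factor (1+rho)/2 in variance. The size of the gain is uncertain because rho is unstated: from 35% of the variance at rho 0.3 to 10% at 0.8. The two readings of d = 0.17 put the gain in standard error at about 4% (rho 0.83) or about 19% (rho 0.32). On the second reading the planned test detects about 0.34 SD, which is larger than the 0.29 cited from the literature if that figure is in outcome SDs. The adjusted model is the safer choice under either reading. The result assumes equal variances at the two visits and a common baseline slope in both arms. This is a free improvement and does not make the planned test invalid.

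**What to change.** State that each Phase III outcome is analysed by a linear model of the 6-month value on randomised arm and the baseline value of that outcome, together with the covariates already planned. In the detection-limit paragraph, give the assumed pre-post correlation and say whether d = 0.17 is in outcome SDs or is derived from f, then restate the detectable difference for the adjusted model. The cost is a sentence or two and one recalculation. It needs no new data, visits or participants, and one degree of freedom per outcome.

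### The Phase III detectable effect of d = 0.17 does not follow from its stated inputs, which give about 0.29; the correlation and the definition of d behind it are not stated

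*Protocol article*

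**What the plan says.** The claim is in the protocol article, Anticipated Results, under Effects of Intervention in Phase III. That paragraph opens with a meta-analytic benchmark: "the estimated combined effect size of physical and cognitive interventions, presented as Cohen’s *d*, is 0.29". It then sets the design values, "considering α = 0.05, a β = 10 and an annual drop-out of 5" per cent, and states that "we will be able to detect in a pre-post repeated measure ANOVA on the different outcomes", with the Flanker effect as the example, "between two groups of 250 participants a small effect *d* = 0.17".

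The Phase III design section gives a six-month intervention, with all participants assessed "at baseline and following the 6-month intervention". That is one pre and one post measurement.

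The paragraph does not give the pre-post correlation, whether the test is one- or two-sided, or which standard deviation scales d.

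**The concern.** In a two-visit repeated-measures ANOVA, the treatment effect is the group-by-time interaction, which is the same test as comparing change scores between arms. Its detectable effect in raw SD units depends directly on the pre-post correlation ρ. A detectable d quoted without ρ cannot be checked. Here the stated inputs alone give a value about 1.7 times the one claimed (0.29/0.17).

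The paragraph places 0.17 directly after 0.29, so a reader will take the trial to have a wide margin over the literature effect. If ρ is moderate, the margin is small or absent, and a null result could be read as excluding effects that the trial had little chance of seeing. The single figure also covers a battery that runs from cognitive tests to imaging and EEG, whose correlations over six months need not be alike.

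**Working it through.** **Inputs.** From Effects of Intervention in Phase III: α = 0.05, β read as 10%, 250 per arm, 5% annual drop-out. From the Phase III design section: six months, one baseline and one post measurement. Assumed: two-sided test, because an ANOVA F test is named. Six months at 5% a year is about 2.5%, or 250 × 0.975 = 243.75 per arm (about 244). Taking the full 5% gives 237.5.

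**Step 1: the stated figure from the stated inputs.** Detectable d = (1.960 + 1.282) × √(2/n).
- n = 250: 3.242 × 0.0894 = 0.290
- n = 243.75: 3.242 × 0.0906 = 0.294
- n = 237.5: 3.242 × 0.0918 = 0.297 (0.298 by the noncentral distribution)

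The stated 0.17 is not reproduced. Variants at n = 250 do not reach it either: one-sided 0.262, 80% power 0.251, both together 0.222. A main effect of group on the mean of both visits gives 0.251 at ρ = 0.5, and no less than about 0.205 for any ρ ≥ 0.

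**Step 2: the correlation that 0.17 needs, with d in raw outcome SDs.**
- Change score or group-by-time: 0.294 × √(2(1 − ρ)) = 0.17, so 1 − ρ = (0.17/0.294)²/2 = 0.167 and ρ = 0.83. The range is 0.83 to 0.84 across 0 to 5% drop-out.
- ANCOVA: 0.294 × √(1 − ρ²) = 0.17, so ρ = √(1 − 0.334) = 0.82. The range is 0.81 to 0.82.

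**Step 3: detectable d and power over assumed ρ** (243.75 per arm, two-sided 0.05). The document gives no ρ, so these values are assumptions.

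| ρ | Detectable d at 90% power, change score | Detectable d at 90% power, ANCOVA | Power for d = 0.17, change score |
|---|---|---|---|
| 0.3 | 0.35 | 0.28 | 35% |
| 0.5 | 0.29 | 0.25 | 47% |
| 0.7 | 0.23 | 0.21 | 68% |
| 0.8 | 0.19 | 0.18 | 84% |

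**Step 4: other meanings of d.**
- If d is scaled by the SD of change, the correlation is absorbed into the scale and the detectable value stays near 0.29 at any ρ.
- If d was taken as 2f from a repeated-measures interaction, the noncentrality is λ = f² × N × m/(1 − ρ) with m = 2 visits. At N = 500 and ρ = 0.3 this gives f = 0.0859 and 2f = 0.172, close to the stated figure. Exactly 0.17 needs ρ of 0.32 (N = 500) to 0.35 (N = 475). In a 2 × 2 interaction each cell mean departs by f SDs, so one arm changes by +2f, the other by −2f, and the difference in change is 4f = 0.344 SD. That is larger than 0.29, not smaller.

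**Step 5: power for the benchmark of 0.29 by change score.** At ρ = 0.5 it is 90.0% (250 per arm), 89.3% (243.75) and 88.5% (237.5), and it rises with ρ. At ρ = 0.3 and 243.75 per arm, 0.29/1.183 = 0.245; 0.245 × √(243.75/2) = 2.71; 2.71 − 1.96 = 0.75, which is about 77%.

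**The case against.** The strongest reply is that a missing input is not an error. An outcome with ρ of 0.83 or more would make 0.17 correct, and nothing shows that the authors assumed less. The only repeat-measure correlations in the article, under Surveys, are at least 0.80 for each sub-scale and 0.89 overall. The article is also a condensed account; it says that exact Phase III details are still under discussion, and a correlation and a named primary outcome can reasonably sit in a fuller document.

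Much of this stands. A reader might infer that the trial's sensitivity has been shown to be overstated. The document does not support that, because neither ρ nor the scale of d is given. The Surveys correlations belong to a self-report questionnaire repeated after about 58 days, so they neither confirm nor exclude 0.83 for a cognitive or imaging outcome at six months. The wording "in a pre-post repeated measure ANOVA on the different outcomes (e.g., Flanker effect" is loose, and need not be a guarantee for each outcome separately. Nor does the article say on what basis the 0.29 was standardised, beyond calling it Cohen's d.

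The reply does not remove the point. The article chose to publish a specific number beside its inputs and a benchmark, and the inputs do not yield it. That is a fault in a stated figure, not an absent detail.

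**Conclusion.** The claim of d = 0.17 at 90% power is unsupported as written. The stated inputs give about 0.29. Reaching 0.17 in raw SD units takes an undeclared correlation of about 0.83 (change score) or 0.81 to 0.82 (ANCOVA). The alternative route through 2f gives a quantity worth about 0.34 SD of difference in change, which cannot be compared with 0.29. The document does not show which route was used.

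This rests on a two-sided test, β meaning 10%, equal arms and drop-out of 0 to 5%. The figure is not disproved for an outcome with a very high correlation.

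A reader might also conclude that the trial is too small. That does not follow: for the effect the article itself cites, power is about 89 to 90% by change score at ρ = 0.5 and higher above that. It falls short only if ρ is clearly lower and change scores are used. The point concerns a stated sensitivity and is of moderate weight.

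**What to change.** Define d on the same scale as the 0.29 and say which standard deviation is used. Remove the single figure for all outcomes. Replace it with detectable effects over assumed correlations at 90% power and about 244 per arm: by change score 0.35, 0.29, 0.23 and 0.19 at ρ = 0.3, 0.5, 0.7 and 0.8; by baseline-adjusted ANCOVA 0.28, 0.25, 0.21 and 0.18. Label the correlations as assumptions, and have the sponsor state the one it relies on for a named outcome, with its source.

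The cost is a sentence or a short table and a less favourable stated sensitivity. The sample size of 500 can stay.

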#### Principal Statistical Analysis

Principal statistical analyses to be performed will include mainly linear regression models in within-subjects and between-groups experimental designs. We may require applying non-parametric statistics in certain cases.

We will also use exploratory data mining techniques like clustering and classifiers in order to identify groups of similar participants and explore the relation between different biologic and lifestyles variables and the different outcomes.

The final aim of this study is to investigate and identify those factors that can promote Brain Health. Considering the binary nature of the end-point of this study (phase I and II), the analysis within the study population will be based on the calculation of odds ratios, hazard ratios and relative risks of exposure to protective factors on the *a priori*-defined 7 pillars of interest. All analyses will be performed correcting for covariate variables (e.g., age, sex, education, income, etc.)

### Pitfalls, Artifacts and Troubleshooting

This study presents various pitfalls and limitations. Similar to all long-term longitudinal studies, participant drop-out is a crucial pitfall that needs to be addressed. In order to minimize participant drop-out we aim to keep participants engaged via strategies described previously (see “BBHI Launching and Recruiting” and “The BBHI Community”). Briefly, we maintain regular communication with participants via social media, periodic public conferences, dissemination of information on recent findings, organization of public events, as well as periodically inviting participants to face to face meetings with the BBHI research and leadership team.

Given the longitudinal nature of the study, another possible pitfall is the possibility for variability in data collection due to instructor bias. To minimize this risk detailed protocols and extensive training is performed by each new member of the research team. Additionally, periodic data quality checks are performed to ensure the quality and reproducibility of the data being collected.

Lastly, as discussed in Section “Characterization of the Cohort,” our cohort is currently not fully representative of the general population for gender (over-representation of women) and educational status (higher than general population). We aim to correct this through ongoing, targeted participant recruitment. Nevertheless, these biases will be considered when analyzing and interpreting and the data.

## Conclusion

The BBHI is a large longitudinal cohort study being conducted in Spain, focused on the promotion of brain health in middle aged adults. The study’s aims are to investigate the biological, environmental and social determinants of brain health maintenance, and whether a multi-dimensional intervention program, focused on life-style habit changes, can have short and long terms effects on cognitive functioning and reduces the incidence of neuropsychiatric brain diseases.

The BBHI will allow us to combine the findings from both a prospective cohort analysis and a randomized-controlled intervention, conducted with the same harmonized measures and outcomes. In line with recent biosocial models of network medicine (Greene and Loscalzo, 2017), the three phases of the BBHI with relate biologic evidence with environmental and social analyses, and enable a deeper understanding of factors promoting healthy aging. Beyond a holistic elucidation of health and disease in aging, the BBHI will investigate if an individualized multi-dimensional intervention program can enhance cognitive functions and reduce the incidence of new future diagnoses. Given the complex interactions of the determinants of individual pathophenotypes (Kivipelto et al., 2013), multi-dimensional interventions and their interactions may yield the best response.

The broad and favorable response to the BBHI, with fast recruitment and high retention rates of a very active cohort, reflects the interest and timeliness of the topic of brain health. Female (66%) and higher-educated (70%) persons are overly represented in the BBHI cohort. This, however, is in line with other longitudinal studies ongoing in Spain (Olazarán et al., 2015). The over-representation of these demographics, possibly reflects the advanced literacy required to complete the surveys (Olazarán et al., 2015) or the increased education on brain health among more educated individuals. Indeed, gender differences in the utilization of health care suggest that women tend to use diagnostic and preventative medicine more than men (Gómez Gómez, 2002).

## Ethics Statement

This study was carried out in accordance with the recommendations of the “Unió Catalana d’Hospitals” with written informed consent from all subjects. All subjects gave written informed consent in accordance with the Declaration of Helsinki. The protocol was approved by the ‘Unió Catalana d’Hospitals.’
